#### Qualitative data

2.9.2

Outcome data related to the implementation strategy and effectiveness of the intervention will also be qualitatively collected through interviews and observation (28).

Interviews: To gain a deeper understanding of the experiences of the mentors and mentees, both parties will be interviewed at the end of the intervention. There is no interview component for the control group participants. The interviews will include questions related to the role of the mentorship, the experience of the mentee, and the perceived effect on the institutions. Mentees will also be asked to reflect on the intervention’s effectiveness on their health and lives. The interviews will follow a semi-structured interview guide (Supplementary material B); they will be recorded and transcribed verbatim.

In terms of design, we will apply the convergent parallel design as we will collect qualitative and quantitative data simultaneously, but we will analyze the data sets separately. The aim of this design is that the data sets will enrich and inform each other. A thematic approach alongside an interpretative phenomenological analysis (IPA) will be used in the qualitative analyses (38, 45). The IPA method will give us access to the lived experiences of the participants and mentors. Data will be analyzed with an inductive-deductive approach. Our theoretical background for this paper will be theories on meaningful integration and health (38, 46, 47). Theories on feasibility and fidelity, implementation, and evaluation will also be applied. The first author will conduct the initial analysis of the data, supervised by the last author. Once this is completed the analyses will be reviewed and modified together with the coauthors (48).

Observations: The first author will conduct systematic observations following a pre-structured checklist (Supplementary material C) for all participants in the intervention group during their placements. The observations will be used to assess the scope of tasks carried out by the participants and the fidelity of the implementation strategy. Each participant will be observed at least once in their working environment and observations will last between 30 and 60 min. A complete overview of the methods and measures of the pilot study is presented in Table 1.

**Table 1 tab1:** Data collection and evaluation method outcomes.

Evaluation method	Evaluation outcome measures
Questionnaire	Self-rated health and other health outcomes, sociodemographic- and migration-related factors
Observations	Fidelity, feasibility, dose of exposure
Individual interviews: participants	Experienced differences on self-rated health and other outcomes, dose received (satisfaction), dose of exposure (participation)
Individual interviews: mentors	Effect on institutions, feasibility, fidelity, dose of exposure (participation)

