### Power calculation and sample size

2.10

This pilot aims to evaluate both the feasibility and effectiveness of the piloted intervention. However, the sample size will probably not be sufficient to rely on statistical significance to address the effectiveness in health outcomes. For reporting the results of the pilot study regarding effectiveness, we will therefore look at trends by using relative risk measures with CI without relying on statistical significance only. If the study is found to be feasible and the trends of effectiveness in a positive direction for the participants, a new study involving a full evaluation of the effect on health as measured by the SRH will require a total sample size of 120 participants with 40 participants in the intervention arm – 20 for each round – and 80 participants in the control arm, based on the assumptions of a 1:2 individually randomized controlled trial with superiority design, with 80% power, 0.05 significance level of assessment, and standard deviation of 1.0 for both arms. The minimum detectable difference between the two arms is calculated to be 0.55.

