### Statistical analysis

2.11

Sociodemographic- and migration-related variables measured at baseline will be described for both the intervention and control arms. Continuous variables will be described with mean, standard deviation, and interquartile range. Categorical variables will be described as counts and percentages (absolute or relative frequency).

We will conduct intention to treat (ITT) analyses. However, it might not always be feasible to obtain information from participants who withdraw from a six-months intervention. As a part of the feasibility exploration, we will try to contact these participants by phone after the intervention period. This will allow us to compare the baselines assessments for those who left the intervention and see if they differ from the rest of the participants.

The effect on health will be measured quantitively regarding changes in self-perceived health for each subject between the intervention and control participants. Based on the questionnaire, SRH scores will be calculated pre- and post-intervention/non-intervention for each participant in both arms. Mean SRH scores will be calculated in both arms and for both time points. Differences in the mean SRH scores at the two time points will be calculated to measure changes in SRH over time. Any difference in SRH change between the two arms will be estimated using both crude (unadjusted) analysis and linear (mixed) regression. We will explore changes in other health and wellbeing assessments in a similar way to determine whether a different measure better detects changes in health. However, we will obtain basic sociodemographic and migration related factors at the baselines questionnaire that will allow us to describe the participants for each of the rounds. In addition, we will collect data on perceived changes in health through qualitative interviews.

Assuming that covariates at baseline are mostly complete, missing outcome values at follow-up due to drop-outs (lost to follow-up) from the study, will be tried corrected for, depending on missingness mechanism, using either simple approaches such as linear regression (Assuming Covariate-Dependent Missing Completely at Random) or more complex approaches [assuming missing at random (MAR)], such as GEE together with multiple imputation or inverse weighting, or using (linear) mixed model approach (using maximum likelihood methods) (49).

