### Evaluation of implementation strategy

2.12

Evaluating an implementation strategy is a complex endeavor for which there is not consensually accepted guidelines (28, 50). Many evaluating components can be included, but in this case, we will focus on feasibility, fidelity, dose received, or satisfaction, and dose of exposure, or participation, as suggested in the guidelines for conducting feasibility and pilot studies for implementation trials (28). In short data on evaluation will be collected through interviews and observations of both participants and mentors following a structured schema for observations and semi-structured interview guides for mentors and participants.

*Feasibility* will be assessed in our study by asking both mentors and participants how they experienced the implementation of the intervention, including the challenges they faced. For mentors, we will ask questions related to the execution of the mentor role. For participants, feasibility will be assessed by asking about the challenges and facilitators related to the placement, both at the personal level and regarding the institutions where they were placed. In addition, feasibility will be assessed through observations at the field.

*Fidelity* will be assessed through observations in the field compared to the study protocol by reviewing our implementation strategy, assessing intervention delivery, and evaluating how the implementation was in line with the purpose of the study and its aims (51).

*Dose received* (satisfaction) is defined as the participants’ satisfaction with the dose of the intervention received and will be assessed through questions to participants regarding the scope of tasks they executed and to which degree they value them in both professional and personal terms (52).

*Dose of exposure* (participation) is defined as the extent to which the participant actively engaged with, interacted with, and was receptive to the intervention. It will be assessed by asking the participants and the mentors about their stay at the institution, the activities they participated in, and their total time spent at the institution.

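### End-of-intervention interviews and a late phone call with no stated feasibility questions may leave early leavers little voice in the feasibility and satisfaction findings, and withdrawal and non-matching are not named as feasibility results

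*Protocol article*

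**What the plan says.** All references are to the protocol article.

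- **Interview timing (2.9.2, Qualitative data).** Of mentors and mentees: "both parties will be interviewed at the end of the intervention". No interview at withdrawal is described.
- **Feasibility (2.12).** It is assessed "by asking both mentors and participants how they experienced the implementation of the intervention, including the challenges they faced". Observation is a second source: "In addition, feasibility will be assessed through observations at the field".
- **Coverage of observations (2.9.2).** "Each participant will be observed at least once in their working environment", during the placement.
- **Dose received, or satisfaction (2.12).** It "will be assessed through questions to participants regarding the scope of tasks they executed". Table 1 lists it under participant interviews and nowhere else.
- **People who withdraw (2.11).** As part of exploring feasibility, "we will try to contact these participants by phone after the intervention period". The use given is a comparison of leavers' baseline assessments with those of the other participants.
- **What follows from the pilot (2.10).** A full evaluation is described under the condition "If the study is found to be feasible and the trends of effectiveness in a positive direction for the participants". The Discussion has a similar condition: feasible and positively experienced.

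**The concern.** A pilot of this kind should show where the implementation strategy fails, and people who leave are the most direct evidence of that. The protocol expects such losses. Section 2.4 reports user representatives' advice on work hours and childcare. Section 2.5 concedes that some matches will be imperfect. The Discussion names loss to follow-up, limited mentor availability, and the possibility that six unpaid months feel too long.

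Yet the main instrument for experience and satisfaction is timed for those who reach the end. The one contact aimed at leavers comes late and has no stated content bearing on feasibility. Neither 2.12 nor Table 1 names withdrawal, failure to find a mentor or failure to start as a feasibility result. If these passages are followed literally, the judgement that the placement was feasible and well received could rest largely on people for whom it worked well enough to stay.

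**Working it through.** The protocol gives no withdrawal rate, satisfaction value or feasibility threshold, so there is no figure of its own to reproduce on this point. Most of the check is a comparison of passages.

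**1. Which sources can reach someone who leaves early?**

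| Source | Where stated | Reaches an early leaver? |
|---|---|---|
| Participant interview (only source for satisfaction) | 2.9.2, Table 1 | Not assured; timed at the end of the intervention |
| Mentor interview | 2.9.2, Table 1 | Not stated either way for mentors of leavers |
| Observation, at least once | 2.9.2 | Only if it takes place before the person leaves |
| Midway evaluation | Discussion | Only if the person is still there; described as a means of keeping engagement and addressing challenges |
| Time spent at the institution (dose of exposure) | 2.12 | Partly; asked of participants and mentors, so it can record a short stay but not the reason for it |
| Phone call | 2.11 | Yes, if reached; only after the intervention period |

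**2. Does the call fill the gap?** Section 2.6 has participants answer the survey for the first time during the three preparation days. Baseline data are therefore held for everyone who attended, and comparing leavers with stayers at baseline needs no call. Only contact could supply reasons for leaving, barriers met and satisfaction, and none of these is stated. The call also comes late: someone who leaves at the end of month 2 of a six-month placement would be called at least 6 − 2 = 4 months later. Neither 2.12 nor Table 1 includes the call, although 2.9.2 presents Table 1 as the full list of methods and measures.

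**3. Do the missing-data methods help?** The intention-to-treat analysis and missing-data approaches in 2.11 concern the questionnaire outcomes. Table 1 does not place satisfaction or feasibility in the questionnaire, so those methods do not reach them.

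**4. Direction and size.** Let *d* be the share who withdraw, *p_C* the share of completers satisfied and *p_L* the share of leavers satisfied. Then:

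- all starters: (1 − *d*)·*p_C* + *d*·*p_L*
- completers only, minus all starters: *d*·(*p_C* − *p_L*)

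The difference is positive when leavers are less satisfied and zero when they do not differ. None of the three inputs is in the documents. On assumed values only, with *p_C* = 80% and *p_L* = 20% to 40%:

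- *d* = 10% (4 of the maximum 40): 0.10 × 0.40 to 0.10 × 0.60 = 4 to 6 points
- *d* = 40% (16 of 40): 0.40 × 0.40 to 0.40 × 0.60 = 16 to 24 points
- *p_L* = 80%, any *d*: 0 points

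This shows only how the mechanism scales. The interviews are to be analysed thematically and by interpretative phenomenological analysis. No satisfaction percentage is planned, so these are not estimates of an error in any reported result.

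**The case against.** A reader might infer that leavers are not heard at all. The text does not support that. Section 2.11 plans to contact them and places the contact within the feasibility work. Observation is intended for every intervention participant, a midway evaluation is mentioned, and time spent at the institution is part of dose of exposure. Only someone who leaves before the on-site contacts would miss them.

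A reader might also infer that leavers' mentors are excluded. The documents neither include nor exclude them. Section 2.6 describes the intervention per participant, so its end could mean the end of that pair's placement. The call's content may be wider than its one stated use: the preceding sentence in 2.11 concerns the difficulty of obtaining information from people who withdraw, so follow-up outcome data may also be intended. The interview guides in Supplementary material B are not shown, and an article may leave participant-flow counts to a fuller document.

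These points narrow the concern but do not remove it. The article itself fixes the interview timing, the sole source for satisfaction, and the timing and stated use of the call. The stated use does not need the call, and the information that would need it is not mentioned. Time at the institution shows that someone left, not why.

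**Conclusion.** The point holds as a limited weakness with an inexpensive remedy. As written, early leavers may contribute little to the feasibility and satisfaction findings, and withdrawal and non-matching are not named among the feasibility results.

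The consequence is conditional. If leavers are less satisfied than completers, the picture is too favourable; if they do not differ, the distortion is zero. Its size cannot be computed from the documents.

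It would go too far to say that the decision on a further trial is shown to be biased upward. There is no numerical decision rule. The condition in 2.10 also requires positive effectiveness trends, which rest on questionnaire data analysed by intention to treat with methods for missing outcomes. What can be said is that one part of the basis for that decision may draw mainly on those who stayed.

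**What to change.** - **2.9.2:** hold the participant and mentor interviews when a pair's placement ends, whenever that is. State that mentors of participants who withdraw are interviewed too.
- **2.11:** make the already planned phone contact soon after withdrawal rather than after the intervention period. State that it asks, on a voluntary basis, about reasons for leaving, barriers met and satisfaction. The baseline comparison can stay; it uses data already held.
- **2.12 and Table 1:** add as feasibility results the numbers eligible, matched with a mentor, started and completed, with reasons for loss at each step. State that these are read together with the interviews when feasibility is judged for the purpose described in 2.10 and the Discussion.

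The cost is revised wording, earlier timing of a contact already planned, and a few short extra interviews. No extra staff are needed. Some leavers will decline, which section 4 entitles them to do; how many were reached should be reported so that readers can see how complete the account is.

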### Power calculation and sample size

2.10

This pilot aims to evaluate both the feasibility and effectiveness of the piloted intervention. However, the sample size will probably not be sufficient to rely on statistical significance to address the effectiveness in health outcomes. For reporting the results of the pilot study regarding effectiveness, we will therefore look at trends by using relative risk measures with CI without relying on statistical significance only. If the study is found to be feasible and the trends of effectiveness in a positive direction for the participants, a new study involving a full evaluation of the effect on health as measured by the SRH will require a total sample size of 120 participants with 40 participants in the intervention arm – 20 for each round – and 80 participants in the control arm, based on the assumptions of a 1:2 individually randomized controlled trial with superiority design, with 80% power, 0.05 significance level of assessment, and standard deviation of 1.0 for both arms. The minimum detectable difference between the two arms is calculated to be 0.55.

### Statistical analysis

2.11

Sociodemographic- and migration-related variables measured at baseline will be described for both the intervention and control arms. Continuous variables will be described with mean, standard deviation, and interquartile range. Categorical variables will be described as counts and percentages (absolute or relative frequency).

We will conduct intention to treat (ITT) analyses. However, it might not always be feasible to obtain information from participants who withdraw from a six-months intervention. As a part of the feasibility exploration, we will try to contact these participants by phone after the intervention period. This will allow us to compare the baselines assessments for those who left the intervention and see if they differ from the rest of the participants.

The effect on health will be measured quantitively regarding changes in self-perceived health for each subject between the intervention and control participants. Based on the questionnaire, SRH scores will be calculated pre- and post-intervention/non-intervention for each participant in both arms. Mean SRH scores will be calculated in both arms and for both time points. Differences in the mean SRH scores at the two time points will be calculated to measure changes in SRH over time. Any difference in SRH change between the two arms will be estimated using both crude (unadjusted) analysis and linear (mixed) regression. We will explore changes in other health and wellbeing assessments in a similar way to determine whether a different measure better detects changes in health. However, we will obtain basic sociodemographic and migration related factors at the baselines questionnaire that will allow us to describe the participants for each of the rounds. In addition, we will collect data on perceived changes in health through qualitative interviews.

Assuming that covariates at baseline are mostly complete, missing outcome values at follow-up due to drop-outs (lost to follow-up) from the study, will be tried corrected for, depending on missingness mechanism, using either simple approaches such as linear regression (Assuming Covariate-Dependent Missing Completely at Random) or more complex approaches [assuming missing at random (MAR)], such as GEE together with multiple imputation or inverse weighting, or using (linear) mixed model approach (using maximum likelihood methods) (49).

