### Intervention

2.6

The intervention for a single participant consists of a six-month assistantship with a personal mentor, matched as explained above, at one of two higher education institutions in Bergen. Through their mentors, the mentees are integrated into the larger educational and research groups at the institutions. The participants in the intervention will first take part in 3 days of preparation for the intervention. Training components include an overall introduction to the study and the educational institutions involved and discussions on challenges that may arise and how to solve them as well as training in cultural competence. They will also sign the informed consent form and answer the survey described below, for the first time.

They will then attend their institutions for a minimum of 2 days per week, taking part in their mentor’s or research group’s daily activities, which may entail meetings, supervision, lectures, and other relevant educational activities with an increasing degree of independence. We will not provide cultural competence training to the mentors, but we will encourage the mentors to utilize and incorporate the participants’ cultural competence at the working place. The mentors will be the primary source of information for the participants at each placement site. The mentor’s role will consist of, among other tasks, to organize a working space, introduce the participants to the other colleagues, include the participants in tailored activities, involve the participant in the group’s daily activities and generally support the participants throughout the period (Figure 1).

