#### Questionnaire

2.9.1

We have developed a questionnaire that all participants will answer twice: in Bergen, participants will complete the questionnaire once pre- and once post-intervention, and participants in the control arm in Kristiansand will also complete the questionnaire twice but with a six-month period between the responses.

The questionnaire is available in Norwegian and English and includes 40 questions with an expected time to complete of 35 min (Supplementary material A). The following questions, which have been used in several cultural settings, will be included in the survey (32–35).

Sociodemographic, sense of coherence and integration: Background questions on sociodemographic and migration factors are adopted from the CHART-study (26, 27). These questions include information about arrival year, emigration reason, educational level and background, marital status, language level, and household members.

The sense of coherence scale with 13 items (SOC-13) is used to measure subjective sense of comprehensibility, manageability, and meaningfulness in one’s life. SOC-13 assesses how people view their life and identifies how they use their resistance resources to maintain and develop good overall health (36–38). Our questionnaire includes 10 questions from the Immigration Policy Lab Integration Index (IPL-12) related to the domains of integration, linguistic integration, and psychological integration (38). Two questions related to income level and understanding of political matters were excluded as they were not deemed to be necessary.

Variables on health and wellbeing: Self-rated health (SRH) is the individual’s own evaluation and perception of their health and is widely used in research related to health disparities in diverse populations. In our study, self-rated health is the main health outcome, assessed by the question: “How do you currently assess your health?” with the possible answers “very poor,” “poor,” “none,” “good,” or “very good.” Furthermore, the question “Do you suffer from long-term (1-year) illness or injury of a physical or psychological nature that impairs your daily life?” and if yes, “How would you describe the impairment in terms of slight moderate or severe?” is included from the Nord-Trøndelag Health Study-3 (HUNT-3) but is not the main outcome (39).

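### Section 2.11 promises intention to treat and a call to withdrawals, but names only a baseline comparison as its use and does not say month-6 self-rated health will be asked

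*Protocol article*

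**What the plan says.** Section 2.11 (Statistical analysis) of the protocol article states: "We will conduct intention to treat (ITT) analyses". It then concedes that "it might not always be feasible to obtain information from participants who withdraw from a six-months intervention", and continues: "As a part of the feasibility exploration, we will try to contact these participants by phone after the intervention period". The stated benefit of that contact is "This will allow us to compare the baselines assessments for those who left the intervention and see if they differ from the rest".

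Two other places bear on this. Section 2.6 (Intervention) says of the preparation days: "They will also sign the informed consent form and answer the survey described below, for the first time". Section 2.9.1 (Questionnaire) says: "We have developed a questionnaire that all participants will answer twice", in Bergen before and after the intervention and in Kristiansand six months apart. SRH, the main health outcome, is one question with five response options.

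The last paragraph of section 2.11 plans to correct for missing follow-up outcomes, with the method depending on the missingness mechanism. The options are linear regression under covariate-dependent missing completely at random (MCAR) or, under missing at random (MAR), GEE with multiple imputation or inverse weighting, or a maximum-likelihood linear mixed model. The effect itself is to be estimated by a crude comparison of SRH change and by linear (mixed) regression.

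**The concern.** The call and its stated purpose do not match. Comparing leavers with stayers at baseline uses data collected before anyone can leave. An intention-to-treat analysis lacks the leavers' outcome, and a call made once the intervention period is over comes at the right time to ask for it. Followed as written, the team could make the call and still come away without that answer.

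Dropout related to the outcome is plausible here. The Discussion expects loss to follow-up and notes that participants may find six months too long for unpaid work that does not advance their accreditation. People may leave because the placement is not helping, because they are unwell, or because they have found work, so the bias could go either way. Section 2.10 lets the direction of the trend, read without relying on significance alone, inform whether a full study follows. A modest spurious shift in mean change could therefore affect that decision. Outcomes not collected at six months cannot be recovered by a later analysis plan.

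**Working it through.** **The plan's own figure.** Section 2.10 gives a detectable difference of 0.55 with 40 intervention and 80 control participants, SD 1.0, 80% power and significance level 0.05. Two-sided, (1.960 + 0.842) × √(1/40 + 1/80) = 2.802 × 0.1936 = 0.543, or 0.547 with the t distribution. The figure reproduces. It belongs to the later randomized trial and does not affect this point.

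**What is held and what is missing for a leaver in Bergen.**

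| Item | Source | Held without the call? |
|---|---|---|
| Baseline SRH and covariates | Section 2.6, preparation days | Yes |
| Leaver-stayer baseline comparison | Stated use of the call, section 2.11 | Yes |
| Month-6 SRH | Second questionnaire, section 2.9.1 | No statement that it is sought after withdrawal |

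**Illustration 1: size of the shift in completers.** The document gives no dropout rate, so these rates are assumptions. Let the true mean change in the intervention arm be 0, with change distributed N(0, 1) in SD units. Let a fraction a drop out among those whose SRH falls and b among the others, with dropout in this arm only. The mean of the positive half of N(0, 1) is √(2/π) = 0.798, so

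completer mean = 0.5 × 0.798 × (a − b) / (1 − (a + b)/2).

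- a = 30%, b = 10% (20% overall): 0.5 × 0.798 × 0.20 / 0.80 = +0.10 SD.
- a = 45%, b = 5% (25% overall): 0.5 × 0.798 × 0.40 / 0.75 = +0.21 SD.

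A simulation of 400,000 draws gives +0.101 and +0.211. Exchanging a and b reverses the sign.

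**Illustration 2: do the planned methods repair it?** Simulation assumptions: 40 and 80 participants, true effect 0, SD 1 at each time point, pre-post correlation 0.5 (so the SD of change is √(2 − 2 × 0.5) = 1), and about 22% dropout in the intervention arm only, more likely at lower SRH. There were 4,000 repetitions. The imputation is a single within-arm regression on baseline SRH, a simple stand-in for the MAR methods. Bias in the estimated effect:

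| Dropout depends on | Completer change score | Baseline-adjusted regression | Imputation from baseline regression |
|---|---|---|---|
| Baseline SRH | −0.12 | 0.00 | 0.00 |
| Unobserved month-6 SRH | +0.12 | +0.19 | +0.20 |

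When dropout depends on baseline, adjustment and imputation work and the crude change comparison does not. When dropout depends on month-6 SRH, all three are biased. With a single follow-up, imputing from baseline SRH adds little to a baseline-adjusted regression of completers.

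**The case against.** A reader might infer that the promised intention-to-treat analysis collapses into a completer analysis. The text does not support that. Section 2.11 lists imputation and a maximum-likelihood mixed model, which can keep leavers in through their baseline data, and weighting, which uses that data to reweight those observed. The first row of the second table shows that such methods can matter. A completer-type result is one permitted outcome, through the crude change analysis or the covariate-dependent-MCAR regression, both of which use observed follow-up only. It is not the necessary one.

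It can also be said that the text never rules out asking SRH on the call. The sentence before it is about obtaining information from withdrawals, section 2.9.1 has all participants answering twice, and an article may leave the content of a call to the full protocol. This stands in part: the authors may intend to ask. But the article does state a purpose for the call, and that purpose is one the call is not needed for.

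The models may also have more than baseline SRH to work with. Baseline includes several mental-health and wellbeing scales, and placement observations, a midway evaluation and mentor reports are planned. These could serve as auxiliary information, though section 2.11 names none of them for that use.

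Two further inferences should be resisted. Section 2.9.2 says that "both parties will be interviewed at the end of the intervention", which does not limit interviews to those who complete, so completer bias in the satisfaction and feasibility data is not shown. Nor should the illustrative shifts be expressed as a share of 0.55, which is the later trial's detectable difference. Finally, the protocol openly says that the pilot cannot establish effectiveness, which limits the consequence.

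**Conclusion.** The point holds as a gap between the intention-to-treat promise and the stated use of the call. The stated comparison needs no call, and no sentence says that month-6 SRH will be sought from those who leave. The planned methods deal with baseline-dependent dropout but not with dropout that depends on the unobserved outcome.

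The size cannot be fixed from the document. Under the assumed patterns the completer mean change in the intervention arm shifts by about 0.10 to 0.21 SD, and the baseline-adjusted and imputed estimates are biased by about 0.19 to 0.20 SD when dropout depends on month-6 SRH. These figures assume no true effect, a roughly normal outcome (SRH has five categories) and dropout in one arm only. Similar dropout among controls would offset part of the shift, and dropout of those doing well would reverse it. This is a worthwhile and cheap correction to data collection, not a flaw that invalidates the pilot.

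**What to change.** State in section 2.11 that the follow-up questionnaire, and at minimum the SRH item, is sought at about six months from everyone with a baseline in either arm, regardless of continued participation and subject to the right to withdraw in section 4. Use the planned call for this among withdrawals, and ask also why they left and how long they attended. Analyse the answers as observed outcomes, and keep the MAR methods for those not reached. The baseline comparison of leavers and stayers can remain, described as an analysis of data already held.

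The cost is one or two extra questions on a call already planned, some additional calls to Kristiansand controls not reached in person (the planned call covers only those who leave the intervention), and a small difference in mode of administration between phone and questionnaire answers. Recording the mode would allow that difference to be described.
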